### Data Safety Monitoring Committee (DSMC) and interim analyses

There will be four interim analyses. The DSMC will conduct the first interim analysis once 50 patients are accrued. For this analysis, the DSMC will be blinded to the identity of each treatment arm, but OS and toxicity data will be presented for each arm (Arm 1 and 2), and treatment doses and volumes will be presented for SAEs reviewed. There are three planned interim analyses for efficacy in addition to the final analysis. The first two interim analyses are expected to be carried out when the total number of observed study deaths reaches 50 and 100, thus treatment details will be reviewed to determine plausible causation of toxicities. As such, interim efficacy analyses will not be blinded. The DSMC will recommend stopping the trial if there is an OS difference that is statistically significant with a threshold of p < 0.001 using the stratified log-rank test. The third interim analysis will be carried out after 50% accrual, or 250 patients to review QoL for Arm A and B. If the analysis yields significant results, we will select the superior arm and assign all patients moving forward to that group for the remainder of the trial duration. However, if results are not significant, we will continue to randomize patients to either Arm A or B until study completion. This will not affect the 1st randomization between Arms 1 and 2.The final analysis is expected to be carried out 3 years after the enrollment of the last subject.

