## Statistical considerations

### Randomization

#### 1^st^ randomization

The study will employ a 1:1 randomization between Arm 1 and Arm 2, with further stratification between 1) systemic therapy within last two weeks (yes vs. no), 2) number of sites to be treated with SABR (one vs. multiple) and 3) SABR to abdominal sites (yes vs. no).

Permuted block randomization will be used to reduce selection bias, promote allocation concealment, and improve balance across groups over the trial period. Patients will be randomized based on a permuted block design using a block size based on a multiple of 3 (with block size known only to statistician until analysis is completed [23]. The Coordinating Centre and trial statistician will be responsible for configuring the module within REDCap, the electronic data capture (EDC) system that will be used to randomize participants.

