#### 2^nd^ randomization

The 2^nd^ randomization of the study will also employ a 1:1 randomization between Arm A and Arm B, with stratification by sex (female vs. male vs. other).

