#### 2^nd^ randomization

The sample size is based on hypothesized QoL differences (mean difference of 5.7) between the intervention arms based on the landmark Basch et al. study, as well as the unpublished standard deviation of 15.6 for EQ-5D-5L scores from our ongoing SABR-COMET-3 study to capture expected standard deviation for our patient population [13, 14]. Group sample sizes of 125 and 125 will provide 80% power to detect a significant difference based on an alpha of 0.05. We will plan an analysis of Arm A and B after 250 patients.

The total sample size for this trial is 598 based on the primary objective of the first randomization.

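### The 250-patient quality-of-life look uses the full planned A vs B sample and alpha but is called an interim with randomization continuing, and its trigger (50% accrual, or 250) contradicts the total of 598

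*Protocol article*

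**What the plan says.** All references are to the protocol article.

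- **Sample size calculation, 2nd randomization.** "Group sample sizes of 125 and 125 will provide 80% power to detect a significant difference based on an alpha of 0.05". The inputs are "hypothesized QoL differences (mean difference of 5.7) between the intervention arms" and an "unpublished standard deviation of 15.6 for EQ-5D-5L scores". The section then plans one analysis of Arms A and B after 250 patients. It gives 598 as the total for the trial, driven by the first randomization.
- **Data Safety Monitoring Committee (DSMC) and interim analyses.** "The third interim analysis will be carried out after 50% accrual, or 250 patients to review QoL for Arm A and B". This look is one of three efficacy interims that come on top of a final analysis, itself expected three years after the last enrolment. If the look is significant, every later patient is assigned to the better arm. If not: "if results are not significant, we will continue to randomize patients to either Arm A or B until study completion".
- **Thresholds.** The only interim threshold in that section is p < 0.001, and it is tied to overall survival. For quality of life it says only that results may be significant or not.
- **Population.** The Abstract and the endpoint section restrict the second randomization to BC Cancer sites. Study design lists institutions in Canada, the United Kingdom, the United States and Australia.

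**The concern.** EQ-5D-5L is the primary endpoint of the second randomization. One section treats 250 patients as the complete sample, carrying all of the alpha. The other treats 250 as an interim point after which the comparison may go on. An analysis at full planned information and full alpha is an interim only if something confirmatory follows, and in that case the alpha has to be shared.

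The decision rule makes this matter. A significant look closes the randomized comparison for good, while a non-significant one leaves it open and more A/B data accrue. If those data feed a second test at 0.05, the endpoint has two unadjusted chances of success.

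The trigger is a separate defect. Half of accrual and 250 patients are different points for a trial of 598, and neither phrase says whether the count covers the whole trial or only patients in Arms A and B. That count decides whether the look has the stated 80% power.

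**Working it through.** **1. The plan's own sample size**

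Inputs: difference 5.7, SD 15.6, alpha 0.05 (two-sided assumed, since sidedness is not stated), power 80%, allocation 1:1.

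n per arm = 2 × (1.960 + 0.842)² × 15.6² / 5.7² = 117.6, so 118; an exact t-test gives 119.

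The stated 125 is slightly larger. It is reached with 5% dropout (118 / 0.95 = 124.2) or a rank-test efficiency factor (119 / 0.955 = 124.6), although the article names neither. Power at 125 per arm is about 82%. So 250 in A/B is the complete planned sample with a small margin, not a part of it.

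**2. Type I error if A vs B is tested twice at 0.05**

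Assumptions: the first test is at 250 A/B patients, the second at the final A/B number N, and both are two-sided at 0.05. Under the null the two statistics are bivariate normal with correlation √(250/N).

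Type I error = 1 − P(|Z1| < 1.96 and |Z2| < 1.96).

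| Final A/B N (assumed) | 250/N | Correlation | Type I error |
|---|---|---|---|
| 275 | 0.909 | 0.953 | 6.4% |
| 300 | 0.833 | 0.913 | 6.9% |
| 360 | 0.694 | 0.833 | 7.6% |
| 400 | 0.625 | 0.791 | 7.9% |
| 598 (ceiling) | 0.418 | 0.647 | 8.6% |

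The article does not state N. For scale, if BC Cancer sites supplied 50% to 60% of 598 (an assumption), N would be 299 to 359 and the error 6.9% to 7.6%. With no second confirmatory test it is 5%.

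**3. The trigger**

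- 50% of 598 = 299.
- 250 / 598 = 41.8%.
- 250 / 250 = 100% of the planned A/B sample.
- 250 is half only of 500, a total the article does not state.

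**4. If 250 counts the whole trial**

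The number per A/B arm is then 125 × (BC Cancer share of the first 250). To keep the 118 per arm that 80% power requires, the share must be at least 118 / 125 = 94%. Any lower share misses the stated power, and the trial recruits in four countries.

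**5. Levels that would hold 5% over two looks**

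| Final A/B N | Equal levels, each look | Lan-DeMets O'Brien-Fleming type: at 250 | at final |
|---|---|---|---|
| 300 | 0.036 | 0.028 | 0.042 |
| 360 | 0.032 | 0.014 | 0.046 |
| 400 | 0.031 | 0.009 | 0.047 |

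**The case against.** The strongest reply is that no sentence says A vs B will be tested again. The sample-size section announces a single analysis. The interim section says that randomization continues and, separately, that a final analysis takes place. It does not say that the final analysis repeats the A/B hypothesis test, or at what level. The 0.05 at the look is also borrowed from the sample-size statement. Nominal levels and spending functions normally sit in a statistical analysis plan or full protocol, and neither is shown here.

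Much of this stands. A reader might infer that type I error definitely rises to 7–9%. The documents do not support that: a second test is implied by the interim label and the continued randomization but never stated, and the top of that range needs nearly all 598 patients in a randomization confined to BC Cancer sites. A reader might also quote a specific power loss at the look, for example 53–61%. That needs 250 to mean whole-trial accrual, which the sample-size section makes the less likely reading, plus an assumed BC Cancer share of 50–60%. Nor do the documents say how many of the 250 would still lack follow-up scores.

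It is fair, too, that moving later patients to the better arm after an adequately powered test is a legitimate design choice, and that the article says the first randomization is unaffected.

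What the reply does not remove is the conflict in the text. One section treats the 250-patient analysis as complete and the other calls it interim, without giving the status of later A/B data. The two halves of the trigger also disagree. An analysis plan could add a boundary, but it would still have to override the protocol's wording on both.

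**Conclusion.** The point holds as a contradiction in the protocol with a conditional error-rate consequence. The status of the 250-patient look (single confirmatory test or first of two) is unresolved, and the trigger is inconsistent with a total of 598 whichever view is taken of alpha.

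If a second A vs B test at two-sided 0.05 is intended, type I error for this primary endpoint is about 6.4% to 7.6% for a final A/B number of 275 to 360, and it cannot exceed 8.6%. If later A/B data are descriptive, it is 5%. These figures rest on the assumed second test, an inferred 0.05 at the look, and an assumed range for the unstated final A/B number. The stated 80% power holds if 250 means patients in Arms A and B with outcome data; it fails on a whole-trial count unless about 94% or more of those patients come from BC Cancer sites.

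The text should be settled before the look takes place, because a significant result ends the randomized comparison.

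**What to change.** 1. **Trigger.** Delete the reference to 50% accrual. State that the look occurs when 250 patients have been randomized to Arm A or B and their primary follow-up EQ-5D-5L assessment is observed or due.
2. **Status of the look.** Choose one option and use it in both the sample-size and the interim-analysis sections.
   - **(a) Single confirmatory test.** Declare the 250-patient analysis the only confirmatory A vs B test, at 0.05, and stop calling it an interim. Describe later A/B data as descriptive and say why randomization continues after a null result.
   - **(b) Two looks.** Prespecify alpha spending over the two looks, for example of Lan-DeMets O'Brien-Fleming type, state the expected final A/B number, and use the first boundary as the criterion for assigning all later patients to one arm.

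Cost: both are wording changes to the protocol and analysis plan. Option (a) needs no extra patients and keeps type I error at 5%. Option (b) means a stricter level at 250, about 0.028 for a final A/B number of 300 or 0.014 for 360, and so less chance of stopping A/B randomization at that point. Neither option touches the first randomization.

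### The 250-patient A versus B quality-of-life analysis is sized as the one full-alpha test but described as an interim look, with no error control if the endpoint is tested again at study end

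*Protocol article*

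**What the plan says.** Two places in the protocol article describe the same analysis differently.

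- **Sample size calculation, 2nd randomization.** The comparison rests on "hypothesized QoL differences (mean difference of 5.7) between the intervention arms" and an "unpublished standard deviation of 15.6 for EQ-5D-5L scores". The result is: "Group sample sizes of 125 and 125 will provide 80% power to detect a significant difference based on an alpha of 0.05". An analysis of A and B is planned once 250 patients are in, which is the whole powered sample.
- **DSMC and interim analyses.** The 250-patient quality-of-life review is listed as the third interim analysis, one of three that come on top of a final analysis. It is placed at half of accrual, equated with 250 patients. The decision rule has two branches. The first is "If the analysis yields significant results, we will select the superior arm and assign all patients moving forward to that group". The second is "However, if results are not significant, we will continue to randomize patients to either Arm A or B until study completion".

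The same section sets a stopping threshold for overall survival, a difference "statistically significant with a threshold of p < 0.001 using the stratified log-rank test". It sets none for the quality-of-life look. EQ-5D-5L quality of life is the primary endpoint of the second randomization, so this is one of the trial's two primary outcomes.

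**The concern.** Under the sample size section, the 250-patient analysis is the test: it has the full sample and the full alpha. Under the interim section, it is a look that can succeed and be acted on, or fail and be followed by more A/B randomization. A reader cannot tell whether a non-significant result at 250 ends the confirmatory question or leaves it open for the final analysis.

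This matters in two ways. If the endpoint gets a second chance at 0.05 after failing once, the error rate attached to an eventual positive claim is higher than stated. And a significant result at 250 ends the randomized A versus B comparison for all later patients, so the threshold at that look should be explicit and agreed before the data are seen.

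**Working it through.** **Inputs from the protocol article.** Mean difference 5.7; SD 15.6; 125 per arm; alpha 0.05; allocation 1:1; analysis at 250; trial total 598. The number of sides is not stated; two-sided is assumed, because a one-sided test would need only 93 per arm. The second randomization is limited to BC Cancer sites and its final number is not given, so it is varied between 250 and 598.

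**1. The plan's own sample size.**
n per arm = 2 × (1.960 + 0.842)² × (15.6/5.7)² = 117.6, so 118 (119 with a t-test). The stated 125 is slightly larger; for example, 118/(1 − 0.05) rounds up to 125, though no such allowance is stated.

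Power with 125 per arm:
- standard error = 15.6 × √(2/125) = 1.973
- 5.7/1.973 = 2.889
- power = Φ(2.889 − 1.960) = 82.3% (82.1% with a t-test)

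The stated 80% is therefore reached at 250 patients using essentially the whole two-sided 0.05.

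**2. Type I error if the endpoint is tested at 0.05 at 250 and again at N.**
Under the null hypothesis the two test statistics are bivariate normal with correlation √(250/N). The overall error is 1 − P(|Z₁| < 1.96 and |Z₂| < 1.96).

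| Final A/B number N | Correlation | Overall two-sided error |
|---|---|---|
| 260 | 0.981 | 5.9% |
| 275 | 0.953 | 6.4% |
| 300 | 0.913 | 6.9% |
| 400 | 0.791 | 7.9% |
| 500 | 0.707 | 8.3% |
| 598 | 0.647 | 8.6% |

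Simulation with 2 million draws gave 6.9%, 8.3% and 8.6% at 300, 500 and 598. The row for 500 is the total implied by equating half of accrual with 250 patients (250/0.5 = 500). Half of the stated trial total would be 598/2 = 299, so the trigger itself is ambiguous. The row for 598 is an upper bound that would need every trial patient to enter A/B.

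**3. What splitting alpha would cost at 250.**
Power at 250 for a nominal two-sided p is Φ(2.889 − z), where z is the matching critical value. The maximum of 400 is an illustration, not a figure from the protocol.

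| Rule | p at 250 | p at end | Power at 250 |
|---|---|---|---|
| Single test at 250 | 0.05 | none | 82% |
| O'Brien-Fleming-type spending, maximum 400 | 0.013 | 0.045 | Φ(2.889 − 2.48) = 66% |
| p<0.001 at 250 | 0.001 | about 0.05 | Φ(2.889 − 3.29) = 34% |

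**The case against.** Several counter-arguments have force.

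- **The second test is not written down.** No sentence says A versus B will be re-tested at study end or at what level, and the final analysis is not tied to this endpoint. A reader might infer that the true error rate of the second randomization is 7 to 9%. The text does not support that as a statement of fact: the figures hold only if a re-test at 0.05 is done. The range is also selective. With few patients added after 250 the error is 5.9% (260) or 6.4% (275), and it cannot exceed 8.6%.
- **Continuing to randomize need not mean re-testing.** The second randomization has secondary endpoints (hospitalization and emergency visits, cost-effectiveness, exploratory overall survival), and the design is factorial. Further A/B patients inform all of these. This stands.
- **A boundary may be in a document not shown.** It may, and the absence of a spending function from an article is not a fault in itself. Nor would every alpha split contradict the stated power: p<0.0407 at 250 still gives 80%, leaving about p<0.020 at the end for a maximum of 400. The common Pocock and O'Brien-Fleming rules would not keep 80% at 250, however (76% and 54% for a maximum of 500).

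What remains is the conflict within the article: one section presents the 250-patient analysis as the full powered test, the other as an interim look before a final analysis, with an action rule but no threshold. An unseen boundary could settle the error rate, but these two descriptions would still need reconciling.

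**Conclusion.** The two sections do not agree on the status of the 250-patient A versus B analysis, and the stated rule gives no error control for a second look at this primary endpoint. The inflation is conditional: with a re-test at two-sided 0.05, the error is between 5% and 8.6% depending on how many A/B patients follow the look, and 8.3% at the total of 500 implied by the interim section. With no second confirmatory test, the error stays at 5% and only the wording needs correcting. The figures assume a two-sided test and an unadjusted threshold of 0.05 at both looks.

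This is a should-fix point. The trial's size rests on the first randomization, and the interim section states that the A/B decision leaves that randomization untouched.

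**What to change.** In the section on the DSMC and interim analyses, state that the 125 + 125 analysis is the only confirmatory A versus B test, at two-sided 0.05, and that A/B data collected afterwards are used for estimation and secondary endpoints only. This keeps the 5% error rate and the stated 80% power and needs no extra patients. The only loss is the right to a second confirmatory test.

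If a second confirmatory test is wanted, fix the maximum A/B number, give the significance level for each look, and restate the power at 250. With a maximum of 400, O'Brien-Fleming-type levels of p<0.013 and then p<0.045 bring power at 250 down from 82% to about 66%. Borrowing the survival threshold of p<0.001 would bring it down to about 34%.

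Either way, replace the double trigger (half of accrual, or 250 patients) with a single number, and settle the rule before the 250th A/B patient, because the result can change allocation.

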## Ethical considerations

The Principal Investigator will obtain ethical approval and clinical trial authorization by competent authorities according to local laws and regulations.

### Institutional review board (IRB) / research ethics board (REB)

The protocol (and any amendments), the informed consent form, and any other written information to be given to subjects will be reviewed and approved by a properly constituted Institutional Review Board (IRB)/Research Ethics Board (REB), operating in accordance with the current federal regulations ICH GCP and local regulatory requirements. A letter to the investigator documenting the date of the approval of the protocol and informed consent form will be obtained from the IRB/REB prior to initiating the study. Any institution opening this study will obtain IRB/REB approval prior to local initiation and will be responsible for maintaining approval throughout the duration of the trial. Principal Investigators must provide evidence of IRB/REB approval on an annual basis.

### Informed consent

The written informed consent form is to be provided to potential study patients should be approved by the IRB/ REB and adhere to ICH GCP and the ethical principles that have their origin in the Declaration of Helsinki. The investigator is responsible for obtaining written informed consent from each patient, or if the patient is unable to provide informed consent, the patient’s legally acceptable representative, prior to beginning any study procedures and treatment(s). The investigator should inform the patient, or the patient’s legally acceptable representative, of all aspects of the study, including the potential risks and benefits involved. The patient should be given ample time and opportunity to ask questions prior to deciding about participating in the study and be informed that participation in the study is voluntary and that they are completely free to refuse to enter the study or to withdraw from it at any time, for any reason. The informed consent must be signed and dated by the patient, or the patient’s legally acceptable representative, and by the person who conducted the informed consent discussion. A copy of the signed and dated written informed consent form should be given to the patient or the patient’s legally acceptable representative. The process of obtaining informed consent should be documented in the patient source documents.

### Confidentiality of subject records

The names and personal information of study participants will be held in strict confidence. All study records (case report forms, safety reports, correspondence, etc.) will only identify the subject by initials and the assigned study identification number. The investigator will maintain a confidential subject identification list (Master List) during the course of the study. Access to confidential information (i.e., source documents and patient records) is only permitted for direct subject management and for those involved in monitoring the conduct of the study (i.e., Sponsors and their representatives, representatives of the IRB/REB, and regulatory agencies). The subject’s name will not be used in any public report of the study.

## Data sharing

Protocol data from this study will be pooled with the pending EORTC trial OligoRARE, a randomized trial specifically looking at the impact of SABR in patients with oligometastases from less-common tumour histologies. Anonymized data from patients with non-breast, non-prostate, non-lung and non-colorectal histologies will be shared with EORTC investigators. 

## Protocol amendments and trial publication

Any modifications to the trial protocol must be approved and enacted by the Principal Investigator. Protocol amendments will be communicated to all participating centres, investigators, IRBs, and trial registries by the principal investigator. Any communication or publication of trial results will be led by the principal investigator and is expected to occur within 1 year of the primary analysis. Trial results will remain embargoed until conference presentation of an abstract or until information release is authorized. Authorship of the trial abstract and ultimately the full manuscript will be decided by the principal investigator at the time of submission. Professional writers will not be used for either abstract or manuscript preparation.

